#### **4.6.2.5. Fertility and embryogenesis**

The role of iNKT cells in embryogenesis, reproduction, and spermatogenesis is not well understood. Mice that lack iNKT cells have normal fertility and pregnancies.

Reproductive toxicology studies have not yet been performed with NKTT120. Subjects of child-bearing potential are required to use appropriate birth control methods. Pregnant and breast-feeding women should not receive NKTT120. Women of child-bearing potential desiring to become pregnant should not receive NKTT120 or should wait for the elimination of NKTT120 from the circulation and the recovery of peripheral iNKT cells before becoming pregnant. The effect of NKTT120 on normal spermatogenesis is unknown.

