#### **4.8. Dose Rationale**

In selecting a starting dose and planned range of doses to be studied, consideration was given to the maximum recommended safe dose (MRSD) calculated using standard approaches (FDA Guidance for Estimating the Maximum Safe Starting Dose in Initial Clinical Trials for Therapeutics in Adult Healthy Volunteers), evaluation of safety factors, and an anticipated pharmacologically active dose (PAD).

The human equivalent dose (HED) to the No Observed Adverse Effect Level (NOAEL) determined in the GLP repeat dose toxicology study in cynomolgus monkeys was 3.2 mg/kg. Using a 10-fold safety factor, the MRSD is 0.32 mg/kg. The HED of an expected PAD is 0.001 mg/kg. Therefore, the planned starting dose of 0.001 mg/kg is 1/300th of the MRSD and 1/3,000th of the NOAEL.

The highest planned study dose of 0.1 mg/kg is 1/3rd of the MRSD. Therefore, the planned dose range provides for an expected margin of safety at the lowest and highest doses. However, as described in [Sections 6.1](#) and [6.6](#) of this protocol, the planned doses may be revised based on the evolving understanding of both safety and pharmacologic activity obtained throughout the study.

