**6.7.1. Stopping Rules**

Enrollment in the study will be stopped and administration of NKTT120 will be halted for all newly enrolled subjects if the SRC detects a potential life-threatening safety signal during the study, including during the long-term follow-up of the subjects, and notifies the sponsor that they recommend stopping of dosing of any additional subjects. Adverse events will be evaluated to determine if they are unanticipated effects of the treatment. These events include, but are not limited to:

1. Serious, medically important or opportunistic infections requiring treatment with parenteral antibiotics (and/or empirical use of antibiotics when subject is admitted to hospital or emergency department for pVOC or other event)
2. Cancers of type or rate unexpected in the adult SCD population.

This is a single dose study, and once enrolled and dosed, subjects cannot be considered removed from study, and all attempts must be made to follow the subject for safety reasons.

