  - History of viral infection(s) requiring ongoing treatment (e.g., HIV, HCV, HBV, HSV type 2)
  - Received any live or attenuated viral immunization within six months prior to enrollment
11. Subject is not up-to-date on CDC-recommended immunizations for adults (see 18.1) or received immunization within one month prior to enrollment
12. Major concurrent illness or medical condition that, in the opinion of the investigator, would preclude participation in a clinical study, including but not limited to:
  - Uncontrolled significant cardiovascular disease or cardiac arrhythmia or clinically relevant abnormal screening ECG
  - Serious event such as stroke, TIA, DVT or PE  $\leq 6$  months prior to enrollment
  - Significant bleeding of any cause  $\leq 6$  months prior to enrollment
  - Psychiatric, behavioral or addictive disorder that, in the opinion of the investigator, would preclude participation in a clinical study
  - Known severe pulmonary hypertension (tricuspid regurgitant jet velocity (TRV)  $\geq 3.0$  m/sec on 2-D echocardiogram or an estimated pulmonary artery systolic pressure  $\geq 40$  mmHg
  - Known severe CNS vasculopathy
  - Interstitial lung disease requiring continuous oxygen or clinically significant abnormal screening CXR or O2 saturation  $< 90\%$  on room air
13. Type 1 or type 2 diabetes

14. History of cancer
15. Known allergy or hypersensitivity to any component of NKTT120 manufacturing or formulation or has previously experienced adverse reaction to protein or biologic therapeutic or experimental agent
16. Pregnant or nursing
17. Subjects of either gender who are not using highly effective method of contraception while on study [Defined as established use of oral, injected or implanted hormonal methods of contraception or placement of an intrauterine device or intrauterine system or barrier methods of contraception such as condom or occlusive cap (diaphragm or cervical/vault caps) with spermicidal foam/gel/cream/suppository\* by subject and/or partner of subject. Also acceptable are males with appropriate post-vasectomy documentation of the absence of sperm and women who are post-menopausal or permanently sterilized (e.g., tubal occlusion, hysterectomy or bilateral salpingectomy)]  
  
\*The use of barrier contraceptives should always be supplemented with the use of a spermicide. Spermicides are not a barrier method of contraception and should not be used alone.

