18. Subject has participated in a clinical trial and received an investigational product within one month, five half-lives or twice the duration of the biochemical or biological effect (whichever is longer) of the investigational product prior to the start of screening for this study
19. History of marrow or stem cell transplant

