### **7.3. Subject Withdrawal Criteria**

#### **7.3.1. Withdrawal of Consent**

Subjects are free to withdraw consent and discontinue participation in the study at any time without prejudice to further treatment. Withdrawal of consent should be in writing. Subjects who withdraw consent immediately after treatment will be asked to remain in the study for safety follow-up for at least 30 days after dosing. These subjects and other subjects who withdraw consent during the follow-up period will be asked to complete the end-of-study (last visit) assessment prior to discharge from the study. Subjects who are enrolled, sign informed consent, but do not receive NKTT120, will be replaced.

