### **11.4. Recording adverse events**

Adverse events spontaneously reported by the subject and/or in response to an open question from the study personnel or revealed by observation will be recorded during the study at the investigational site. Clinically significant changes in laboratory values, blood pressure, and pulse need not be reported as AEs. However, abnormal values that constitute an SAE must be reported and recorded as an AE. Information about pre-existing signs and symptoms will be collected from the time the subject signs an informed consent form. AEs will be collected from the first administration of study drug until the end of the study. SAE information will be collected from administration of study drug until their EOS visit, which is 30 days following the recovery of iNKT cells in the peripheral circulation. The AE term should be reported in standard medical

terminology when possible. For each AE, the investigator will evaluate and report the onset (date and time), resolution (date and time), intensity, causality, action taken, serious outcome (if applicable), and whether or not it caused the subject to discontinue the study.

Intensity will be assessed according to the CTCAE grading scale version 4.03.

It is important to distinguish between serious and severe AEs. Severity is a measure of intensity whereas seriousness is defined by the criteria in Section 11.2.1.2. An AE of severe intensity may not be considered serious.

In principle, pregnancy and the lactation period are exclusion criteria for clinical studies involving investigational drugs that are not directly related to the respective conditions. Should a pregnancy occur during this study, it must be reported and recorded on the pregnancy form and the subject should be followed in the study until one month after recovery of iNKT cells and during the entire course of the pregnancy and postpartum period. All recommendations described in the [Investigator Brochure](#) pertaining to pregnancy and lactation must be carefully considered. Pregnancy in itself is not regarded as an AE unless there is a suspicion that an investigational product may have interfered with the effectiveness of a contraceptive medication.

The outcome of all pregnancies (spontaneous miscarriage, elective termination, normal birth or congenital abnormality) must be followed up and documented even if the subject was discontinued from the study.

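### Required contraception has no minimum period after dosing, so a subject discharged after early withdrawal at about Day 30 may stop with much of the dose still present

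*Protocol*

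**What the plan says.** Section 7.2, item 17, excludes "Subjects of either gender who are not using highly effective method of contraception while on study". Section 8.2.1 lists birth control among the medications needed to take part and gives no duration.

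For a completer, the study ends one month after iNKT cells are detectable again (Synopsis, Duration of treatment; Sections 6.2.2 and 6.3.2.1). No drug-level condition applies. For a subject who withdraws consent immediately after treatment, Section 7.3.1 says the subject "will be asked to remain in the study for safety follow-up for at least 30 days after dosing". Those who withdraw later are asked only for the end-of-study assessment before discharge.

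Section 4.6.2.5 states that "Reproductive toxicology studies have not yet been performed with NKTT120" and that the effect on spermatogenesis is unknown. It requires birth control of subjects of child-bearing potential, with no end date. Women who wish to conceive should not receive the drug, or "should wait for the elimination of NKTT120 from the circulation and the recovery of peripheral iNKT cells before becoming pregnant".

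**The concern.** Section 4.6.2.5 names two conditions before pregnancy: the drug is gone and iNKT cells are back. The required contraception period is tied to being in the study. For completers that reflects the second condition. For early withdrawals it reflects neither.

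This is a first-in-human antibody with no reproductive toxicology, so what is at stake is conception, by a female subject or a male subject's partner, while drug is still present. Men have only the on-study rule, because the waiting advice is addressed to women. There is little backstop: Table 3 schedules no pregnancy test after Day 0, and the pregnancy-reporting text in Section 11.4 concerns pregnancies during the study. The point is one of subject protection rather than of statistical analysis.

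**Working it through.** The protocol gives no figure for drug remaining at study end, so there is none to reproduce. The check compares the end of required contraception with a simple first-order decline.

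**Inputs**
- Half-life: about 22 days estimated in humans, 11 days in monkeys (Section 4.9).
- Doses: 0.001, 0.003, 0.01, 0.03 and 0.1 mg/kg (Section 6.1).
- Reference amount: "The HED of an expected PAD is 0.001 mg/kg" (Section 4.8).
- Early discharge: Day 30, the floor in Section 7.3.1.
- Assumptions: first-order decline throughout. No assay limit is given, and target-mediated clearance would lower the results.

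**Formula:** fraction left = 0.5^(t / half-life).

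**1. Withdrawal with discharge at Day 30**
- 22 days: 0.5^(30/22) = 0.389.
- 11 days: 0.5^(30/11) = 0.151.

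| Dose (mg/kg) | Left, 22 d (mg/kg) | Multiple of 0.001 mg/kg | Left, 11 d (mg/kg) | Multiple of 0.001 mg/kg |
|---|---|---|---|---|
| 0.001 | 0.00039 | 0.39 | 0.00015 | 0.15 |
| 0.003 | 0.0012 | 1.2 | 0.00045 | 0.45 |
| 0.01 | 0.0039 | 3.9 | 0.0015 | 1.5 |
| 0.03 | 0.012 | 12 | 0.0045 | 4.5 |
| 0.1 | 0.039 | 39 | 0.015 | 15 |

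Monkeys given 0.1 or 0.3 mg/kg began to show measurable iNKT cells only at week 10, or Day 70 (Section 4.4). At Day 30 in the higher cohorts, both conditions in Section 4.6.2.5 could therefore be unmet.

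**2. Completer at 0.001 mg/kg**
- Section 6.6 bases this dose on a monkey dose that gave 50% depletion, with return to 80% of baseline by day four.
- If humans behave the same way, the end-of-study visit falls between Day 30 (cells never undetectable) and Day 44 (recovery recorded at Day 14, plus 30).
- Fraction left at 22 days: 0.389 to 0.5^(44/22) = 0.250. At 11 days: 0.151 to 0.5^(44/11) = 0.0625.
- The largest residual is 0.001 × 0.389 = 0.00039 mg/kg, below the expected active dose.

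**3. Completer at 0.1 mg/kg**
- Section 6.2.2 puts recovery at six months or more, so the end-of-study visit is at about 180 + 30 = Day 210.
- 0.5^(210/22) = 0.0013, or 0.13%. There is no gap.

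**4. Five half-lives as a minimum**
- 5 × 22 = 110 days; 0.5^5 = 0.031.
- After 0.1 mg/kg: 0.1 × 0.031 = 0.0031 mg/kg, about three times the expected active dose. Five half-lives is therefore not enough alone at the top dose.

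**The case against.** **The subject is already covered.** Section 4.6.2.5 requires birth control without an end date and gives women a stricter waiting condition than any fixed number of days. This stands as far as it goes, and it is why a reader who infers that the protocol contradicts itself would be wrong: advice that runs past the study is compatible with a requirement that stops at its end. But the advice is undated, sits in background text and does not reach men.

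**Low-dose completers.** A reader might infer that these subjects routinely stop contraception with active drug on board. The documents do not support that. Section 6.2.2 forecasts that in the lower cohorts iNKT cells return after the drug has become undetectable, with the final visit a month later still. The Day 30 to 44 timing is an extrapolation from monkeys, and even then the residual at 0.001 mg/kg is below the expected active dose. Since the forecast is not a condition for ending the study, this remains a minor secondary case.

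**Dosed subjects are not let go.** Section 6.7.1 says "once enrolled and dosed, subjects cannot be considered removed from study" and asks for every attempt to follow them. Day 30 is a floor, so discharge then is a worst case. Even so, Section 7.3.1 permits it, and Section 6.7.1 sets no contraception period.

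**The multiples overstate activity.** A reader might take 39 times the expected active dose as evidence of harm. It is not: comparing a decayed residual with a bolus dose is only a rough scale. Section 4.6.2.5 also notes that mice lacking iNKT cells have normal fertility and pregnancies.

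**Other documents may supply the period.** Section 11.4 says that Investigator Brochure recommendations "pertaining to pregnancy and lactation must be carefully considered". The Brochure and the consent text are not available here, so the gap is established for the protocol text only.

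**Conclusion.** The concern holds in a limited form. The operative contraception requirement has no minimum period after dosing, and early withdrawal is where this matters. At discharge on about Day 30, about 39% of the dose remains at a 22-day half-life, or 15% at 11 days, and in the higher cohorts iNKT cells may still be depleted.

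The size rests on first-order decline, on a human half-life that is itself an estimate, and on discharge at the earliest time the protocol contemplates. No hazard is demonstrated. The change is worth making because it costs little and reproductive toxicity is unstudied. Confidence is medium, mainly because the Brochure and consent text cannot be checked.

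**What to change.** - **Section 7.2, item 17, and Section 8.2.1:** have both sexes agree at consent to use contraception until the later of the end-of-study visit and at least five estimated half-lives after dosing. That is 110 days at the 22-day estimate, to be lengthened if the observed human half-life is longer. Five half-lives is already one limb of the washout rule in item 18. That rule concerns prior investigational products, so it is a precedent rather than a derivation.
- **Section 7.3.1:** state that subjects who withdraw early are advised to continue for the same period.
- **Section 4.6.2.5:** cross-refer to this period and keep the condition to wait for iNKT recovery as well, given the 0.0031 mg/kg left at 110 days after 0.1 mg/kg.
- **Consent text:** explain the period there.

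No visit, sample or assay is added. The cost is an instruction that runs past the end-of-study visit or discharge for some subjects, by up to about 110 − 30 = 80 days if either falls at Day 30. After withdrawal it can only be advised.

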### **7.3. Subject Withdrawal Criteria**

#### **7.3.1. Withdrawal of Consent**

Subjects are free to withdraw consent and discontinue participation in the study at any time without prejudice to further treatment. Withdrawal of consent should be in writing. Subjects who withdraw consent immediately after treatment will be asked to remain in the study for safety follow-up for at least 30 days after dosing. These subjects and other subjects who withdraw consent during the follow-up period will be asked to complete the end-of-study (last visit) assessment prior to discharge from the study. Subjects who are enrolled, sign informed consent, but do not receive NKTT120, will be replaced.

#### **7.3.2. Failure to Return for Follow-Up**

Subjects who do not return for follow-up will be considered lost to follow-up. The appropriate clinical site personnel should attempt to contact these subjects by telephone, mail or email in order to obtain information about the reason(s) for discontinuation and information about potential AEs.

The Investigator will provide a written report, collect all EOS data and will complete the Subject Completion/Discontinuation Section of the eCRF.

## 8. TREATMENT OF SUBJECTS

### 8.1. Description of Study Drug

**Table 4: Investigational Product**

|                                | Investigational Product Description                                                  |
|--------------------------------|---------------------------------------------------------------------------------------------|
| Product Name:           | NKTT120                                                                                     |
| Dosage Form:            | 10/mg/mL in 20 mM sodium acetate buffer, pH 5.0, containing 6% trehalose and 0.02% Tween-80 |
| Route of Administration | IV                                                                                          |
| Physical Description    | Clear, colorless solution, essentially free of particulates                                 |
| Manufacturer            | DSM Biologics B.V.                                                                          |

### 8.2. Concomitant Medications

#### 8.2.1. Required Medications

The following medications are required for participation in the clinical study:

1. Immunizations recommended by CDC for adults, unless contraindicated for subject (18.1)
2. Birth control: Barrier (condom or diaphragm) plus spermicide, intrauterine device (hormonal or copper); or oral (combination or single agent) or injectable/implanted hormonal contraceptive

#### 8.2.2. Permitted Medications

All concurrent medications prescribed for SCD or other medical conditions must be at stable doses for at least three months prior to enrollment the study. The following medications are permitted but not required during the study:

- Hydroxyurea (stable dose for two months prior to dosing)
- Antibiotic prophylaxis
- Vitamin D
- Calcium supplement
- Medications for treatment of hypercholesterolemia or hypertriglyceridemia (i.e., statins)

- Pain medications including: NSAID, non-narcotic analgesics, short-acting opioids, long-acting opioids
- Anti-hypertensives: e.g., angiotensin converting enzyme inhibitors, aldosteronereceptor blockers
- Inhaled SABA
- Corticosteroid (oral or inhaled), prednisone (or prednisone equivalent), 10 mg/day.
- Therapies to treat neuropathic pain such as: antidepressants (amitriptyline and nortriptyline), anticonvulsants (gabapentin (Neurontin®) pregabalin (Lyrica®), carbamazepine, felbamate, valproic acid, clonazepam and phenytoin)
- Medications to treat study-emergent adverse events

### **8.2.3. Prohibited Medications and Treatments**

The following medications and treatments are prohibited for the duration of the trial:

- Routinely scheduled blood transfusions as part of chronic blood transfusion therapy
- Erythropoietin
- Corticosteroids (oral, parenteral or inhaled), greater than 10 mg/day prednisone or prednisone equivalent)
- Any experimental agent or drug
- Any broadly immunosuppressive drug or biologic
- Homeopathic medications, unless approved by the investigator

### **8.3. Randomization and Blinding**

This is an open-label study. No randomization or blinding will be required.

## 9. STUDY DRUG MATERIALS AND MANAGEMENT

### 9.1. Study Drug

NKTT120 is a novel recombinant, humanized, IgG1κ mAb that selectively binds to the human iTCR on a subset of T cells called iNKT cells. NKTT120 binds exclusively and specifically to Vα24-Jα18 gene-rearranged iTCRs on human iNKT cells, resulting in depletion of iNKT cells.

NKTT120 is formulated as a clear colorless solution, essentially free of particulates, at a concentration of approximately 10 mg/mL in 20 mM sodium acetate buffer, pH 5.0, containing 6% trehalose and 0.02% Tween-80. All excipients are generally recognized as safe (GRAS) and found in other FDA-approved IV products at equivalent or higher concentrations.

NKTT120 is aseptically filled into USP Type 1 clear glass vials, each closed with a polymer-coated butyl rubber stopper and capped with aluminum caps. Each 3 mL vial of NKTT120 contains 1 mL drug.

This product is for single-use only and will not contain a preservative. It should be stored frozen at -20° C and thawed just prior to use or thawed in refrigerator overnight. The thawed vial should be used for preparation of dose within two hours if kept at room temperature and within 24 hours if refrigerated. Prepared doses must be infused immediately after preparation. Refer to the Pharmacy Manual for further drug preparation and dosing information.

### 9.2. Study Drug Packaging and Labeling

The packaging and labeling will be performed by the Sponsor's packaging and labeling Vendor according to all local legal and regulatory requirements.

Each box will contain between six and nine vials. The number of vials in each box will be identified on the box label. The box label will also indicate the Retest Date of drug contained within the box. The Retest Date will be revised annually based on data gathered from an ongoing stability study.

Refer to the Pharmacy Manual for a description of the drug vial and carton labels.

### 9.3. Study Drug Storage

Study drug will be shipped directly to each clinical site from the NKT Therapeutics Inc. distribution center.

NKTT120 must arrive frozen at the clinical trial site. Upon receipt of a shipment of NKTT120, the site staff will immediately inspect the condition of the shipping containers and the vials to ensure the shipping container has no damage, the gel packs are frozen, the vials are not damaged and TempTale® 4 is not alarmed during shipping. If any of the vials are damaged or have thawed during shipment, the site will document the damage on the drug accountability record and notify NKTT immediately of the problem. **Damaged or defrosted vials cannot be used for the study. Authorization and instructions for destruction and/or return of the damaged Study Drug will be provided in writing by NKTT.** Refer to the Pharmacy Manual for detailed instructions.

Upon receipt, the vials of NKTT120 should be stored upright in a monitored -20°C freezer until required for use.

